### Randomization

After the completion of eligibility screening and baseline assessments, participants will be randomly allocated in a 1:1 ratio to either the supervised multicomponent exercise group or the health education control group. Before randomization, participants will be stratified according to frailty status, classified as prefrail or frail based on the EFS, to promote a balanced distribution of frailty levels between groups.

The randomization process will be performed using the online platform Research Randomizer by an independent researcher who will not participate in participant recruitment, assessments, intervention delivery, or data analysis [27]. Allocation concealment will be ensured through sequentially numbered, opaque, sealed envelopes prepared in advance by the independent researcher.

After baseline assessments, the next sequential envelope will be opened by a research assistant who is not involved in outcome assessment procedures. Participants will then be informed of their assigned group and referred to the corresponding intervention procedures.

### Blinding

This study is characterized as a single-blind RCT with blinded outcome assessment. Participants and physiotherapists responsible for the supervised exercise sessions and health education workshops cannot be blinded to group allocation. However, outcome assessors and data analysts will remain blinded throughout the study to minimize assessment and analysis bias. The researcher responsible for the randomization process will not participate in participant recruitment, baseline or follow-up assessments, intervention delivery, or statistical analyses. Participants will be instructed not to disclose their group allocation to the assessors during the evaluation procedures.

### Interventions

#### Study Procedures

Both groups (intervention and control) will undergo baseline and postintervention testing in a randomized order to ensure an unbiased assessment of the outcomes. Participants in both groups will be instructed to continue with their usual care routines and daily activities throughout the duration of the trial.

#### Intervention Group

Participants in the intervention group will engage in a supervised physical exercise program based on the Vivifrail protocol [21]. The program will span 12 weeks, with sessions held twice weekly, totaling 24 sessions, each lasting approximately 45 minutes, and will include exercises targeting strength, balance, mobility, gait, flexibility, and functional endurance. The sessions will be conducted in small groups under the direct supervision of trained physiotherapists, as described in Figure 2.

**Figure 2. F2:**
[figure not shown]
Exercises used in group 1 (intervention) based on the Vivifrail protocol [21].

The exercise program will be supervised by trained physiotherapists and will be conducted on-site at the CONVIVER Community Center. Participants will be advised to wear comfortable clothing and footwear and to maintain proper hydration throughout the intervention. Each session will be documented in a field diary, which will record the session date, participant compliance (whether they completed the full series or if the session was interrupted), any adverse events (AEs), and their descriptions.

The frequency of 2 supervised sessions per week was selected based on the previous clinical trials involving frail and prefrail older adults that demonstrated significant improvements in functional performance, balance, mobility, and frailty-related outcomes using similar exercise frequencies. Chittrakul et al [23] reported positive effects of a multicomponent exercise intervention performed twice weekly on fall prevention and quality of life in prefrail older adults. Likewise, Bray et al [22] observed improvements in physical performance and functional capacity using a supervised multicomponent exercise program delivered 2 times per week in prefrail older women. Furthermore, recommendations derived from the Vivifrail program emphasize that the exercise prescription for frail older adults should prioritize safety, adherence, and individualized progression and that clinically meaningful benefits can be achieved with supervised exercise performed at least twice weekly. Therefore, the selected frequency was considered appropriate to balance effectiveness, safety, and adherence in this vulnerable population.

Exercise intensity and progression will be individualized according to the participants’ baseline functional capacity, frailty level, and clinical tolerance. Perceived exertion during exercise sessions will be monitored using the Borg Rating of Perceived Exertion scale, aiming to maintain exercise intensity between 11 and 13 points (light to somewhat hard intensity) [28].

Physiological responses and clinical symptoms, including excessive fatigue, dizziness, pain, dyspnea, and cardiovascular symptoms, will also be monitored throughout the sessions to ensure participant safety. Progression of the exercise program will occur gradually throughout the intervention period according to individual adaptation and tolerance. Strength exercises will be progressed by increasing the number of repetitions when participants demonstrate adequate performance and safety. Balance and mobility exercises will be progressed through the reduction of external support.

To ensure intervention fidelity and reproducibility, all physiotherapists involved in the intervention will receive standardized training regarding exercise prescription, progression criteria, monitoring procedures, and safety management before the beginning of the trial. Standardized exercise protocols and progression checklists will be used throughout the intervention period. Attendance will be recorded at each session, and adherence rates will be monitored continuously. Any adaptations, interruptions, AEs, or deviations from the intervention protocol will be systematically documented by the research team.

#### Control Group

Older adults allocated to the control group will participate in a series of workshops focused on healthy aging–related topics. These workshops will be conducted on-site at the CONVIVER Community Center and will provide educational content and practical guidance aimed at promoting health, autonomy, self-care, and quality of life among older adults. Topics addressed during the workshops will include healthy lifestyle habits, fall prevention, chronic disease management, nutrition, medication use, mental health, sleep quality, and strategies to maintain independence during aging.

The workshops will occur twice weekly in parallel with the intervention group activities, with each session lasting approximately 45 minutes (Figure 3). This comparator was selected because the CONVIVER center routinely offers health education and social support activities as part of standard community care for older adults. Therefore, participants allocated to the control group will continue receiving usual community-based care and social interaction throughout the study period.

**Figure 3. F3:**
[figure not shown]
Topics of lectures and workshops conducted in the control group.

The use of an educational control group was chosen to allow for a comparison between a structured supervised exercise intervention and a nonexercised intervention focused on health promotion, while minimizing complete inactivity and maintaining participant engagement during the trial. This strategy also seeks to reduce ethical concerns related to the withdrawal of social and educational support in a vulnerable older population.

In addition, after the completion of postintervention assessments and study procedures, participants allocated to the control group will be invited to participate in the supervised multicomponent exercise program offered by the research team. This delayed-access strategy was adopted to ensure ethical balance and to provide all participants with the opportunity to benefit from the exercise intervention after the conclusion of the trial.

To monitor potential contamination related to external physical activity during the intervention period, participants from both groups will be instructed not to initiate new structured exercise programs outside the study protocol. Physical activity behavior will be monitored through self-reports.

### Outcome Measurements

#### Assessment Procedures

During the screening phase, participants will sign the informed consent form and undergo an eligibility assessment, cognitive screening using the MMSE, and frailty classification using the EFS (Figure 4).

**Figure 4. F4:**
[figure not shown]
Schedule of assessments for screening, sample characterization, and primary outcomes. CFVI-20: Clinical-Functional Vulnerability Index-20; EFS: Edmonton Frailty Scale; FES-I: Falls Efficacy Scale-International; GDS-15: Geriatric Depression Scale-15; IPAQ: International Physical Activity Questionnaire; MMSE: Mini-Mental State Examination; 6MWT: 6-Minute Walking Test; TUGT: Timed Up and Go Test.

At baseline, sociodemographic and clinical data will be collected, along with assessments of depressive symptoms (Geriatric Depression Scale-15 [GDS-15]), muscle mass (calf circumference), physical activity level (International Physical Activity Questionnaire [IPAQ]), fear of falling (Falls Efficacy Scale-International [FES-I]), and clinical-functional vulnerability (Clinical-Functional Vulnerability Index-20 [CFVI-20]) to characterize the older adults. The primary outcomes, namely functional mobility assessed by the Timed Up and Go Test (TUGT) and functional capacity assessed by the 6-Minute Walk Test (6MWT), will be evaluated at baseline and reassessed after the 12-week intervention period (T2).

#### Screening Measurements

##### Cognitive Functional Status

The MMSE will be used to assess cognitive functional status. It is an instrument designed for the initial screening of mental status to evaluate the presence of cognitive deficits. It includes 2 categories of responses: verbal and nonverbal. The MMSE consists of 30 categorical questions. The original scoring of the test classifies cognitive impairment as follows: 30 to 26 (preserved cognitive function); 26 to 24 (suggestive alterations of cognitive impairment); and 23 or below (cognitive impairment). For this study, a cutoff score of 19 will be applied [29-31].

##### Frailty Status

Frailty status will be assessed using the EFS, a multidimensional instrument validated for use in older adults. The scale evaluates domains including cognition, general health status, functional independence, social support, medication use, nutrition, mood, continence, and functional performance [25]. Scores range from 0 to 17 points, with higher scores indicating greater frailty. In this study, participants scoring 5 to 6 points will be classified as prefrail, whereas those scoring ≥7 points will be classified as frail. Individuals scoring 0 to 4 points will be considered nonfrail and will not be included in the trial [26].

### Other Measurements

#### Sociodemographic and Clinical Data

Sociodemographic and economic data, along with general health and lifestyle habits, were collected using a structured form developed by the researchers. This section of the assessment includes various items aimed at capturing key aspects of the participants’ personal and health-related characteristics. The form includes the following data points: name, date of birth, race, marital status, number of children, education level, source of income, monthly income in terms of minimum wage, self-perceived health status, self-reported chronic diseases, presence of depressive symptoms (assessed using the GDS-15), and muscle mass (measured using calf circumference).

#### Depressive Symptoms

The emotional state of participants will be evaluated using the GDS-15 [32,33]. The GDS-15 consists of 15 questions with “Yes” or “No” responses, scored 0 or 1 depending on the question. The total score ranges from 0 to 15 points. In this study, symptoms of depression will be considered present in individuals scoring 6 or more points.

#### Muscle Mass

This will be evaluated through calf circumference measurement. The technique involves asking the participant to stand upright with feet 20 cm apart. Using a nonelastic tape measure, the maximum circumference of the calf is measured perpendicular to its longitudinal axis. Values below 34 cm in men and 33 cm in women indicate reduced muscle mass [34,35]

#### Physical Activity Status

The IPAQ will be applied at baseline to characterize participants’ habitual physical activity levels, and postintervention measurements will be used exclusively for contamination monitoring and not as efficacy outcomes. It consists of 8 open-ended questions about the time spent on moderate- and vigorous-intensity physical activities and sedentary activities (sitting) in a typical week [36]. Based on the IPAQ scoring protocol, participants will be classified into 4 physical activity levels according to the frequency, duration, and intensity of weekly physical activity: inactive, insufficiently active, active, or very active.

Participants classified as inactive will report no regular physical activity lasting at least 10 continuous minutes during the week. Individuals classified as insufficiently active will report some physical activity but will not achieve the minimum recommended levels. Participants classified as active will meet the recommendation of at least 150 minutes of moderate-intensity physical activity per week, 75 minutes of vigorous-intensity activity per week, or an equivalent combination of both. Those classified as very active will exceed the minimum recommended physical activity levels according to the IPAQ scoring criteria [37].

#### Fear of Falling

Fear of falling will be evaluated using the FES-I. The scale comprises 16 questions addressing concerns about falling during daily tasks such as cleaning, cooking, reaching for objects on the floor or overhead, and climbing stairs or ramps. Scores range from 16 to 64, where 16 indicates no concern about falling, and scores above 17 suggest some degree of concern [38-40].

#### Clinical-Functional Vulnerability

Functional decline vulnerability will be assessed using the CFVI-20 [41]. This instrument comprises 20 questions across 8 sections: age, self-perceived health, functional disability, cognition, mood, mobility, communication, and comorbidities. Scores range up to 40, with higher values indicating greater vulnerability. Classifications are as follows: 0‐6 (robust), 7‐14 (potentially frail), and 15+ (frail).

### Primary Outcomes

#### Risk of Falls

Risk of falls will be assessed using the TUGT. The test requires a stopwatch, a chair, and a measuring tape. Participants sit on a chair, and the procedure is explained. They are asked to stand, walk to a line 3 meters away at a self-selected but safe pace, turn around, walk back, and sit down again. Lower times indicate better performance and ≤20 seconds indicates risk of falls [42-44].

#### Functional Capacity

Functional capacity will be measured by the 6MWT following the American Thoracic Society (ATS) protocol [45]. After completion, the same measurements will be repeated, and the total distance walked will be recorded. This procedure will occur pre intervention and post intervention, and results will be compared to a predicted value to assess changes in functional capacity: 6MWD (6-minute walk distance) = 890.46 – (6.11 × age) + (0.0345 × age²) + (48.87 × gender) – (4.87 × BMI), where the 6MWD equation estimates walking distance in meters based on age (in years), gender (1=male, 0=female), and BMI (kg/m²) [46]. It accounts for age-related decline, sex differences, and body composition effects on functional capacity [47].

### Sample Size

Sample size estimation was performed using G*Power software (version 3.1.9.7; Heinrich Heine University) [48,49]. The calculation was based on the primary outcomes of functional capacity and fall risk, assessed by the 6MWT and the TUGT, respectively. An effect size of 0.56 was adopted based on the findings of Espejo-Antúnez et al [50], who evaluated the effects of a 12-week exercise intervention on functional capacity and fall-related outcomes in older adults. Assuming a 2-group parallel RCT design, a statistical power of 95%, and a significance level of 5% (*α*=.05), the minimum required sample size was estimated at 35 participants per group. Therefore, the study was designed to include 70 participants, with 35 allocated to each group. Because recruitment will be conducted among community-dwelling older adults regularly attending activities at the CONVIVER Community Center, and eligibility will depend on screening procedures, the final sample will be obtained through convenience sampling. Recruitment feasibility was considered during the planning phase to ensure attainment of the target sample size.

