### Statistical Analysis

For the statistical analysis, data normality will be assessed using the Shapiro-Wilk test and Q-Q plots. Descriptive statistics will be performed to characterize the sample. Categorical variables will be presented as absolute and relative frequencies, whereas continuous variables will be expressed as means and SDs or medians and IQRs, in addition to graphical representations. Changes in mean values over time will be represented by delta values (Δ).

The primary analytical model for the 2 primary outcomes (6MWT and TUGT) will be an analysis of covariance, comparing postintervention values between groups while adjusting for the corresponding baseline values. Preintervention and postintervention comparisons will be conducted using the 2-tailed paired Student *t* test for normally distributed variables or the Wilcoxon signed-rank test for nonnormally distributed variables. Between-group differences will be analyzed using the independent Student *t* test for normally distributed variables and the Mann-Whitney *U* test for nonparametric variables.

Effect sizes will be calculated using eta squared (η²) and Cohen *d* and interpreted as small (0.2), medium (0.5), or large (0.8). All losses to follow-up and their respective treatment durations will be recorded for intention-to-treat analysis. All participants will be reassessed after the 12-week intervention period whenever possible. Missing data will initially be explored to determine the pattern and mechanism of missingness. When appropriate, missing outcome data will be handled using multiple imputation methods based on chained equations. Sensitivity analyses will be conducted to compare the results obtained from complete-case analyses and imputed datasets in order to evaluate the robustness and consistency of the findings. In addition, per-protocol analyses will be performed as secondary sensitivity analyses to assess the influence of adherence to the intervention on study outcomes. A significance level of *P*<.05 will be adopted for all statistical tests. Statistical analyses will be performed using the SPSS, version 25.0 (IBM Corp) [51], and graphs will be generated using R software (R Foundation for Statistical Computing) [52].

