### Safety Assessment and Withdrawal

Participant safety will be monitored throughout the intervention period by the research team and supervising physiotherapists. Any AEs potentially associated with the exercise sessions or assessment procedures, including dizziness, pain, excessive fatigue, musculoskeletal discomfort, falls, cardiovascular symptoms, or any other clinical complaints, will be immediately documented and evaluated.

If a participant develops any AE or clinical instability during the intervention period, exercise participation will be temporarily interrupted, and the participant will be closely monitored by the research team. When necessary, the participant will be referred for medical evaluation before resuming study activities. In cases where symptoms persist, recur after reintroduction of the intervention, or compromise participant safety, the participant may be withdrawn from the study after clinical assessment by the investigators. All AEs and safety-related occurrences will be systematically recorded in standardized monitoring forms throughout the trial period.

Participants will be free to discontinue their participation at any moment and for any reason, including the option to request the removal of their data from the study. Individuals will be considered withdrawn if they formally request to leave the trial or are lost to follow-up. Participants allocated to the intervention group will be classified as withdrawn if they discontinue participation in the supervised exercise program. Participants allocated to the control group will be classified as withdrawn if they discontinue participation in the educational workshops before the completion of the study.

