The protocol outlined in this study includes a comprehensive range of exercises designed to address frailty and its associated risks holistically. Activities such as multidirectional walking, stepping over obstacles, sit-to-stand transitions, and balance tasks on stable and unstable surfaces aim to improve muscle activation, postural control, and functional capacity [57]. Furthermore, the inclusion of cognitive-motor tasks, such as walking while performing dual tasks, seeks to enhance executive function and reduce fall risk, which are critical for this population [58].

Despite all these, this study protocol may present several potential limitations. First, the single-center design could limit the generalizability of the findings to other populations or settings. The relatively small sample size, although adequately powered for the primary outcomes, might reduce the ability to detect smaller effect sizes or subgroup differences. Additionally, the expected predominance of female participants, which reflects the demographic profile of the community center, could restrict the applicability of the results to older male adults. Finally, the absence of long-term follow-up will limit conclusions regarding the sustainability of the intervention’s effects over time. These potential limitations should be considered when interpreting the future findings and in the design of subsequent studies.

If proven effective, this supervised multicomponent intervention may serve as a practical and accessible public health approach to promote functional resilience and reduce fall-related morbidity in vulnerable older populations. Ultimately, the findings from this study may inform evidence-based recommendations and guide future exercise programs and health policies aimed at improving the quality of life and well-being of frail and prefrail older adults living in the community.

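### The number randomised equals the plan's own stated minimum of 35 per group, with no allowance for the losses it foresees, so the 95% power claim has no margin

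*Protocol article*

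**What the plan says.** The Sample Size section takes its effect from a cited 12-week exercise study ("An effect size of 0.56 was adopted based on the findings of" that study). It continues "Assuming a 2-group parallel RCT design", and sets "a statistical power of 95%, and a significance level of 5"%. It concludes that "the minimum required sample size was estimated at 35 participants per group. Therefore, the study was designed to include 70 participants, with 35 allocated to" either arm. The abstract and the Results section repeat 70 randomised, 35 and 35. The only remark on reaching the target concerns recruitment feasibility; retention is not mentioned.

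Other sections prepare for missing outcomes:

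- **Statistical Analysis:** "All losses to follow-up and their respective treatment durations will be recorded for intention-to-treat analysis". Reassessment at 12 weeks is qualified as being done where possible, and multiple imputation by chained equations is planned, with complete-case comparisons.
- **Safety Assessment and Withdrawal:** participants may be withdrawn for safety or lost to follow-up. Also, "Participants will be free to discontinue their participation at any moment and for any reason, including the option to request the removal of their data".
- **Anticipated Findings (Discussion):** "The relatively small sample size, although adequately powered for the primary outcomes, might reduce the ability to detect smaller effect sizes or subgroup differences".

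**The concern.** A minimum required number is the number that must supply an outcome. Here the same number is used for those randomised, and no step lies between the two. The article therefore makes its power claim for 35 per group while describing how it will handle having fewer.

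At stake is how a non-significant 6MWT or TUGT result would be read. Under a stated 95% power and a general statement of adequacy, such a result invites the conclusion that the programme has no worthwhile effect. The plan does not protect the number on which that reading depends.

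**Working it through.** **Inputs from the article.** Effect size 0.56, type not stated. It is read here as Cohen d, the standardised mean difference that the Statistical Analysis section also names. Alpha 0.05, power 95%, two parallel groups, 1:1 allocation, 35 per group. Sidedness is not given for the sample size; the only mention is "2-tailed paired Student" *t* test in the analysis section. Two-sided is taken here.

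**Assumptions.** Loss of about 9% to 20% (32, 30 and 28 of 35 per group) and a baseline-to-post correlation r of 0.5 to 0.8. The article gives neither.

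**Step 1: the plan's own figure.** By normal approximation, n per group = 2(1.960 + 1.645)² / 0.56² = 82.9, so 83; the exact t calculation gives 84. The stated 35 is not reproduced. Other readings do not give it either:

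- one-sided two-group test: 70 per group;
- 0.56 read as Cohen f in a two-group ANOVA: 44 in total;
- paired or one-sample t test: 44 two-sided, 36 one-sided.

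**Step 2: attrition alone, taking 95% at 35 per group at face value.** The two-sided t test has noncentrality d√(n/2) on 2n − 2 degrees of freedom. Solving for 95% at n = 35 gives d = 0.874. The same d and the printed 0.56 at smaller n give:

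| Per group analysed | Loss | Power, d = 0.874 | Power, d = 0.56 |
|---|---|---|---|
| 35 | 0% | 95.0% | 63.7% |
| 32 | 9% | 93.1% | 59.7% |
| 30 | 14% | 91.5% | 56.9% |
| 28 | 20% | 89.5% | 53.9% |

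Attrition costs 1.9 to 5.5 points at face value and 4.0 to 9.8 points at d = 0.56. The base shortfall at full retention is larger: 95 − 63.7 = 31.3 points.

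**Step 3: the planned ANCOVA at d = 0.56.** The effective standardised difference is 0.56/√(1 − r²), with 2n − 3 residual degrees of freedom.

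| Assumed r | Effective d | 35 | 30 | 28 | n per group for 95% |
|---|---|---|---|---|---|
| 0.5 | 0.65 | 76% | 69% | 66% | 64 |
| 0.7 | 0.78 | 90% | 85% | 82% | 44 |
| 0.77 | 0.88 | 95% | 92% | 90% | 35 |
| 0.8 | 0.93 | 97% | 94% | 93% | 31 |

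**Step 4: inflation alone.** Keeping 35 completers needs 35/0.90 = 38.9, so 39 randomised per group at 10% loss, and 35/0.80 = 43.75, so 44 at 20%. That returns the trial to the row of 35 in Step 2 and the column of 35 in Step 3, not to 95%.

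**Step 5: imputation.** There is one baseline and one post-intervention value. Imputing a missing post value from group and baseline adds essentially no information on the treatment effect beyond the observed pairs. Data removed at a participant's request cannot be imputed.

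**The case against.** Several points on the other side are fair.

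- **The loss is small and its rate is unknown.** At face value, power stays near 90% even at 20% loss. Follow-up is a single 12-week assessment in regular attendees of the centre, and nonadherent participants stay in the intention-to-treat analysis where possible. This stands, and it limits the weight of the point.
- **ANCOVA may supply a margin.** With a correlation of 0.8, 31 per group still give 95%. This also stands. A reader might infer that any loss must push true power under 95%; the article does not support that, because it states no correlation. It supports only that any loss falls below the article's own minimum.
- **The base calculation is the larger problem.** Agreed. A reader might infer that 95% is reached if nobody is lost. The printed inputs do not support that: full retention gives 63.7% by two-sided t test (75.0% one-sided), and ANCOVA reaches 95% only from an unstated correlation of about 0.77.
- **The full protocol may hold an attrition assumption.** Possibly. But the article prints a stated minimum and a number randomised, and the two are identical, so no allowance could lie between them.
- **Imputation and sensitivity analyses are planned.** They address bias and keep participants in the analysis, but they do not restore the lost information.

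**Conclusion.** The point holds in a limited form. The article randomises exactly its stated minimum, foresees losses and leaves no margin. Attrition alone costs about 2 to 5.5 points of power if 35 per group is accepted as giving 95%, under assumed losses of 9% to 20%. That is modest, but it compounds a base figure that 0.56 does not reproduce: about 84 per group are needed by two-sided t test, and between 64 and 31 by ANCOVA as the assumed correlation runs from 0.5 to 0.8. The unqualified statement of adequate power in the Discussion is therefore not supported as it stands. These figures rest on reading 0.56 as Cohen d, on a two-sided 5% test and on equal losses in the two groups. Nothing in the article shows that losses will reach any particular level.

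**What to change.** Keep 70 randomised. In the Sample Size section:

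- state an expected 12-week loss and the assumed baseline correlation;
- say that 35 per group is the number randomised, not the number analysed;
- replace the 95% with the power of the primary ANCOVA at the expected completers, for example 30 and 28 per group, over a range of correlations as in the second table;
- do not count imputed participants as restoring the planned number.

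In the Discussion, make the statement of adequate power conditional on those assumptions. Make the change together with the correction of the base calculation (type of effect size, test and sidedness). Enrolling 39 to 44 per group would not by itself restore 95% power.

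The cost is a few sentences and a less favourable stated power. No extra participants or procedures are needed, and the article says recruitment had not started at submission.

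### The stated 95% power with 35 per group does not follow from an effect size of 0.56: a two-sided two-group comparison has about 64% power.

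*Protocol article*

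**What the plan says.** The Sample Size section of the protocol article gives a complete set of inputs and an output:

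- Effect: "An effect size of 0.56 was adopted", taken from a published 12-week exercise study in older adults. The section does not say whether this is Cohen *d*, Cohen *f*, a between-group effect or a within-group effect.
- Design and power: "Assuming a 2-group parallel RCT design, a statistical power of 95"%.
- Error rate: "and a significance level of 5"%, with sidedness not stated.
- Result: "the minimum required sample size was estimated at 35 participants per group", hence 70 in total.

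The Randomization section fixes equal allocation. The Statistical Analysis section makes a baseline-adjusted ANCOVA the primary model for both primary outcomes, the 6-Minute Walk Test and the Timed Up and Go Test. It reads effect sizes against benchmarks of 0.2, 0.5 and 0.8. The Discussion (Anticipated Findings) calls the sample relatively small, "although adequately powered for the primary outcomes".

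**The concern.** An effect of 0.56 is only slightly above the medium benchmark of 0.5. Detecting it with 95% power in two independent groups normally takes well over 35 per group. If the figure is wrong, the trial's only justification of its size is wrong, and the Discussion repeats the error as reassurance. At a true power of 64%, a real effect of the planned size would be missed about one time in three (1 − 0.64 = 0.36). At the claimed 95%, it would be missed one time in twenty. Readers who accept the claim would over-interpret a null result.

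**Working it through.** **Inputs.** Effect 0.56, two parallel groups, α = 0.05, power 0.95 and n = 35 per group come from Sample Size; 1:1 allocation comes from Randomization. I read 0.56 as Cohen *d* because the Statistical Analysis section uses the 0.2/0.5/0.8 scale. Sidedness is not stated, so both are tried.

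**Attempt to reproduce 35 per group.** For two independent means the noncentrality is δ = d·√(n/2), with 2n − 2 degrees of freedom. Power is the probability that a noncentral *t* exceeds the critical value.

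| Test | n per group | δ | Critical *t* | Power |
|---|---|---|---|---|
| Two-sided | 35 | 0.56·√17.5 = 2.343 | 1.995 | 63.7% |
| Two-sided | 84 | 0.56·√42 = 3.629 | 1.974 | 95.0% |
| One-sided | 35 | 2.343 | 1.668 | 75.0% |
| One-sided | 70 | 0.56·√35 = 3.313 | 1.656 | 95.1% |

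The normal approximation agrees:

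- Two-sided: n = 2(1.960 + 1.645)²/0.56² = 2(12.996)/0.3136 = 82.9, so 83.
- One-sided: n = 2(1.645 + 1.645)²/0.56² = 2(10.824)/0.3136 = 69.0, so 70 after rounding up.

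With 35 per group, two-sided 95% power requires d of about 0.87.

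**Other readings of the same inputs.**

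- Mann-Whitney, two-sided: 88 per group; 62% power at 35.
- α halved to 0.025 for two primary outcomes: 98 per group; 52% power at 35.
- 0.56 as Cohen *f* (equivalent to d = 2 × 0.56 = 1.12): 44 in total, 22 per group; 99.6% power at 70.
- Paired *t* test: 36 pairs one-sided (35 pairs give 94.5%), 44 pairs two-sided. This is a within-group test, not the stated design.

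None gives 35 per group for a two-group comparison. Two near matches may explain the error. The one-sided per-group figure of 70 equals the stated total, and the one-sided paired figure of 36 is close to 35. The text does not show which, if either, occurred.

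**Planned ANCOVA.** Adjusting for a baseline that correlates r with follow-up raises the effective effect to d/√(1 − r²), with 2n − 3 degrees of freedom. The article gives no r, so a range is assumed. The column for 30 per group assumes a 14% loss (5/35).

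| Assumed r | d/√(1 − r²) | Power, 35 per group | Power, 30 per group |
|---|---|---|---|
| 0.5 | 0.647 | 76% | 69% |
| 0.6 | 0.700 | 82% | 76% |
| 0.7 | 0.784 | 90% | 85% |
| 0.8 | 0.933 | 97% | 94% |

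Reaching 95% needs r of about 0.77 with no losses, or about 0.81 with 30 per group.

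**Two primary outcomes.** If both had to be significant, and they were independent with the same effect, power at 35 per group would be about 0.823² = 68% at r = 0.6 and 0.898² = 81% at r = 0.7. It would be somewhat higher if the outcomes are positively correlated.

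**The case against.** The strongest reply is that 64% is the power of an unadjusted *t* test, whereas the primary model is an ANCOVA. Repeated walking and mobility tests can correlate strongly, and at r of 0.77 or above 35 per group does give 95%. That is correct, and it means 95% is not shown to be impossible for the planned analysis. But the Sample Size section neither invokes ANCOVA nor states a correlation, and zero loss would also be needed.

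A second reply is that the effect-size measure is not named. The 0.2/0.5/0.8 scale is given for reporting results, and eta squared is mentioned beside it. Read as Cohen *f*, the trial would be amply powered. This makes the 64% conditional on the *d* reading, but it does not rescue the calculation: under *f* the stated minimum would be 22 per group, not 35.

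Third, the Discussion already concedes that the sample is small and may miss smaller effects. That is fair, but the same sentence still asserts adequate power for the primary outcomes.

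Finally, allowance for losses and for two outcomes may be set out in a fuller document. Those points are secondary here. The finding rests on stated inputs that conflict with a stated output.

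**Conclusion.** The concern holds. No two-group calculation tried on the stated inputs alone, one-sided or two-sided, yields 35 per group for 95% power. With 0.56 as Cohen *d*, the requirement is 84 per group two-sided or 70 one-sided, and the planned 35 gives 64% or 75%. Under the planned ANCOVA, power lies between about 76% and 97% for assumed correlations of 0.5 to 0.8 with no losses, so 95% depends on an unstated and favourable correlation. Enrolment equals the stated minimum, so any loss to follow-up lowers these figures. The non-reproducibility is certain; the 64% rests on the *d* reading and a two-sided unadjusted test. The Discussion's claim of adequate power is unsupported as written. This should be corrected before recruitment starts.

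**What to change.** In Sample Size:

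1. Say whether 0.56 is Cohen *d* or *f*, and whether it is a between-group or a within-group effect in the source study.
2. State the test and its sidedness.
3. Replace the 95% claim with the power that 70 participants deliver: 64% for a two-sided *t* test at d = 0.56, followed by a short table for the planned ANCOVA by assumed correlation, expected loss and the chosen α rule for two primary outcomes.

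In the Discussion (Anticipated Findings), delete the statement of adequate power or tie it to the stated correlation and loss.

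The cost is rewording in two places and a less favourable power figure. No extra participants are needed for the correction. Recruitment had not begun at submission, so the sponsor could still raise the target if it wants 95% power.
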